| 4. Subject of the study and its objectives; statement of the hypotheses, separated into main and secondary hypotheses, and of the clinical parameters (primary and secondary endpoints) against which the hypotheses are to be tested. | Patients with atraumatic abdominal pain have a very broad range of diagnoses, therefore, those patients with atraumatic abdominal pain should receive faster, safer and more targeted care.  To assure high quality of care and potentially reduce mortality, it seems imperative to implement a novel management pathway, which standardizes the process from start of care to final diagnosis, disposition and specific therapy of atraumatic abdominal pain patients in the emergency department (ED). Therefore, a team of multidisciplinary experts has developed the „Abdominal Pain Unit“(APU) treatment process based on the Delphi method. With APU care is structured according to symptoms and processes rather than diagnosis. The implementation of a new structured, symptom-based process is necessary because patients present themselves in the ED primarily with a symptom and not with an already existing diagnosis. In this way, the indication quality of the diagnostics carried out is improved and patients can be treated more quickly and efficiently.  This study aims to improve German ED care for patients suffering from atraumatic abdominal pain. An application-supported pathway for the ED will be implemented, which supports quick, evidence-based, and standardized diagnosis and treatment plans for patients with atraumatic abdominal pain in the ED.  We hypothesize that the App-based APU-process will lead to:  1) Shorter duration of treatment at the ED while improving patient-reported outcomes (assessed as acute pain score or/and patient satisfaction) at discharge from the ED; or an  2) Improvement of patient-reported outcomes (assessed as acute pain score or/and patient satisfaction) at discharge from the ED while measuring a constant duration of treatment; or a  3) Shorter duration of treatment and unchanged patient-reported outcomes (assessed as acute pain score and patient satisfaction) at discharge from the ED.  All three scenarios will be interpreted as improvement of patients care by the new pathway.  Primary outcomes:  Acute pain score at discharge from the ED, patient satisfaction at discharge from the ED, duration of treatment in the ED  Secondary outcomes:  Patient safety, process quality, quality of care |

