| 10. Description of planned measures/examination methods and any deviations from the measures/examinations commonly used in medical practice (what is "routine", what is done differently in the study?).  If validated questionnaires are used in the study, please state the name of the questionnaires and where they are published (references).  Please include non-validated questionnaires as an attachment | The present study is a mixed-methods multicenter trial in 10 hospitals with EDs.  Intervention:  Prior to the study, a pilot study will be conducted over a period of 3 months to test study material and processes. Then, all 10 study sites in this multicenter stepped-wedge cluster randomized controlled trial (cRCT), will start in the control phase and will then consecutively (every 4 months 1 cluster (2 study sites) will start the intervention phase) be enrolled into the intervention arm over a trial period of 24 months. 5 cluster with 5 different  Control:  During the control phase, case as usual in the ED is provided to all patients with atraumatic abdominal pain. Current care as usual of atraumatic abdominal pain patients in the ED is not always evidence-based and might differ significantly from hospital to hospital. Furthermore, the accuracy of the implementation of these recommendations for action is often dependent on the experience and intuition of the attending physician.  Deviation from the standard procedure during the intervention phase:  In the APU treatment process, common treatment guidelines are applied without changing their core content.  Patients with atraumatic abdominal pain should receive faster, safer and more targeted care. This is achieved by implementing a new care process that is structured according to symptoms and processes rather than diagnosis.  The app-supported APU-process (in the following and for clarity, the term APU-process will be used) starts with a patient who suffers from atraumatic abdominal pain presenting in the ED. By means of the APU-app, physicians will be supported in making a structured decision for the subsequent diagnostic and treatment process. Eventually, the APU treatment process ends with either the discharge of the patient with a sufficiently accurate diagnosis from the ED or the patient being admitted to another hospital unit for further treatment. Patients with a shock syndrome or sepsis leave the path for special intensive care early.  The first step in the APU treatment process includes a medical history, a medical examination, measurement of blood parameters, and pain management for patients with atraumatic abdominal pain.  In a second step, a re-evaluation will lead to a decision whether the patient will be discharged from the ED to ambulant care (i.e. in case of unsuspicious clinical findings) or if further diagnostic measures have to be taken. Thus, in a third step, the patient will receive a sonography, however, in the case of persistently unclear clinical findings, in a fourth step, either additional imaging methods will be used, such as computer tomography or magnetic resonance imaging, or a multi-disciplinary consultation and if necessary a patient observation for a few hours will be performed. Patients with worsening medical condition will leave the path for intensive care.  The implementation of a new structured, symptom-based process is necessary because patients present themselves in the ED primarily with a symptom and not with an already existing diagnosis. In this way, the indication quality of the diagnostics carried out is improved and patients can be treated more quickly and efficiently.  This treatment process is to be presented with software support using an app. The app serves as a contemporary means of presenting the process and at the same time as documentation software in the context of the application of the new treatment pathway. The app itself has no influence on the care process, nor does it dictate to the physician using the app how the treatment/therapy is to be carried out.  It merely displays its content and documents whether the user has taken note of the relevant information. It expressly does not serve the purpose of device-based detection, prevention, monitoring, treatment or alleviation of diseases. It does not represent artificial intelligence and does not make decisions for the user at any time. The decision is still the responsibility of the attending medical staff. Thus, the app is a documentation software in the context of process optimisation through the APU treatment process.  The focus of this study will be the new APU treatment process and NOT the approval of the app as a medical device, but the evaluation and possibly approval of the new APU treatment process.  The app receives information manually entered by the treating medical staff. This information includes a patient identifier, patient’s name and age.  The aim of the new process is to avoid unnecessary therapeutic or diagnostic steps and, through the standardised structure. Moreover, the novel APU treatment process aims to prevent important findings from being overlooked or urgently needed measures from being omitted. The focus here is on pointing out the various diagnostic and therapeutic measures without making a final recommendation. The APU treatment process aims to be a work through in the treatment process of patients with atraumatic abdominal pain, similar to a checklist.  The process has so far been presented as an event process chain (EPC). The schematic representation can be found in appendix 4  The treatment procedure is thus more standardised and objectified compared to the "routine procedure".  The evaluation of the study follows a mixed methods approach. Quantitative and qualitative primary data will be triangulated with secondary data from the hospital information system and billing data from the participating health insurance funds. Furthermore, expert interviews are planned.  The evaluation is conducted according to five different modules at different points in time:  - Module 1 (patient-reported primary data): Control and intervention groups will be interviewed via tablet computer (if necessary as paper-pencil) upon discharge from the ED (survey t0). If patients cannot be interviewed in the ED (e.g. due to a transfer to the surgery room), a follow-up survey can be conducted up to 72 hours after the initial contact in the ED on the treatment ward to which the patient is transferred. After 30 days, a telephone follow-up or an online survey is conducted (t1). Patients will be contacted in advance by phone or e-mail to remind them of the follow-up. The analyses include current pain score (numerical rating scale (NRS)), satisfaction with own health and quality of life (items taken from EUROHIS-QOL-8; appendix 2: (Schmidt, Mühlan et al. 2005)), socio-demographic data, as well as patient satisfaction ((ZUF-8) appendix 3 (Schmidt, Wittmann et al. 2002)) and life satisfaction ((Short Scale Life Satisfaction-1 (L-1) appendix 4 (Beierlein et al. 2014.)). See appendix t0 and t1 questionnaire.  - Module 2 (primary data of care): Clinical parameters (e.g. vital signs, previous illnesses, onset of pain, accompanying symptoms, medication history) and the duration of the stay in the ED are recorded for each patient. The data collection takes place without participation of the patients after their discharge from the ED.  - Module 3 (secondary hospital data): For patients with abdominal pain during the study period, the data available for them is extracted from the hospital information system (HIS). The HIS data include, for example, blood parameters, diagnostic examinations and results, diagnoses, procedures, operations and the hospital history (wards, intensive care unit, length of stay, complications, mortality, DRGs, billing figures) of the patients. The data collection is carried out by study staff without the involvement of the patients after their discharge from the ED.  - Module 4 (secondary data of the health insurance company): By declaring their participation in the study, patients agree to transmission of their health available billing data from the statutory health insurance company to the evaluating institute in accordance with §75 of the German Social Code Book V. The transmitted data includes both, the outpatient and inpatient service areas one year before the index stay as well as a period of 30 days after the initial contact. The data can be analysed longitudinally. Important parameters are the development over time in the form of disease progression, mortality and the services used. Furthermore, all patients treated during the study period are identified in the data of the participating statutory health insurance companies and also analysed internally (at the participating health insurance company) with regard to the costs incurred before and after hospitalisation.  - Module 5 (expert interviews, participant observation): Within the framework of participant observation, 5 patients in each of 5 hospitals will be followed after the establishment of the abdominal pain units over the period of their ED stay (n=25). The observation starts with the start of treatment and ends with the discharge from the ED. The observations, which also include the spoken word, are systematically documented in the form of protocols. Furthermore, 2 expert interviews will be conducted per hospital after the introduction of the Abdominal Pain Unit within the project period (total n= 20). The expert interviews will be conducted as semi-structured interviews, recorded on tape and transcribed.  References:  Schmidt, J., et al. (2002). Fragebogen zur Messung der Patientenzufriedenheit. Diagnostische verfahren in der psychotherapie. Göttingen: Hogrefe.  Schmidt, S., et al. (2005). "The EUROHIS-QOL 8-item index: psychometric results of a cross-cultural field study." European Journal of Public Health 16(4): 420-428.  Beierlein et al. (2014). Eine Single-Item-Skala zur Erfassung der Allgemeinen Lebenszufriedenheit: Die Kurzskala Lebenszufriedenheit-1 (L-1). GESIS-Working Papers 2014 \| 33. GESIS: Köln. |

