| 15. Biometric planning with indication of statistical methodology, including power calculation.  Indication of the statistician(s)  (if advice is given by the Institute of Biometry of the Charité, a signature must be inserted) | Justification of the selected case numbers/sample sizes (power calculation).  In the evaluation of a new form of care with a broad focus on improving patient care, there is no single research hypothesis to be tested, but rather a series of combined endpoints (process times, patient-related endpoints). Therefore, no classic sample calculation is possible, as it is usual for confirmatory effectiveness studies. Furthermore, the achievable number of patients is limited by the study centers and the expected proportion of emergency patients with atraumatic abdominal pain. The justification of the sample size is therefore based on feasibility considerations and accordingly a power analysis was performed for relevant endpoints of evaluation modules 1 and 2. A total achievable sample size of 2.000 patients is expected. With a conservative estimate, we expect a loss to follow-up of 15%, since the time of transfer for patients, as well / or the time of outpatient discharge is not always predictable. Moreover, the recording of the endpoints may not be possible in the case of emergency transfers. This means that the expected number of evaluable patients is reduced to at least n=1.700. For the correction of the stepped-wedge design according to Hemming (appendix 4: (Hemming and Taljaard 2016) the following assumptions were made: there are random cluster effects, fixed time effects, but no interactions between cluster and time. Intracluster correlation coefficients (ICC) are usually between 0.01 and 0.02 in human studies (appendix 5: (Killip, Mahfoud et al. 2004). Choosing the conservative variant of an ICC of 0.02, which leads to the highest SWD correction factor on this interval, we obtain a correction factor of 2.71. Applying this correction factor results in an effective total number of cases corresponding to an RCT design of n=627, i.e. n=313 per treatment arm. For the power estimates, the significance level for 3 parallel tests according to Bonferroni is adjusted to α*=0.05/3=0.0167. For the above-mentioned primary endpoints under the respective assumed effect sizes δ and α*, the following numbers of cases would result for an RCT: 1) for δ=0.341 in a 2-sided t-test, n=183 per group, 2) for δ=0.0863 in a Chi² test, n=105 per group, and 3) for δ=0.499 in a 2-sided t-test, n=86 per group are required. The power calculations lead to the result that the study is sufficiently powered for all 3 endpoints with an RCT-equivalent of n=313 patients per treatment arm when testing the 3 test hypotheses defined above. Specifically, a power of 1) 96%, 2) 99% and 3) 99% could be achieved for the assumed effect sizes with the achievable number of cases n=313 per treatment arm corrected for SWD. Especially for the "patient reported outcomes" of endpoints 2 and 3, the assumed number of cases and thus the achievable power would make the adjustment of the evaluations for do not exclude potential confounders such as age and gender from the outset. Power calculations and power estimates were performed with nQuery Advisor 7.0.  Statistician:  [name], Institut für Biometrie und Klinische Epidemiologie, Charité – Universitätsmedizin Berlin  References:  Hemming, K. and M. Taljaard (2016). "Sample size calculations for stepped wedge and cluster randomised trials: a unified approach." Journal of Clinical Epidemiology 69: 137-146.  Killip, S., et al. (2004). "What is an intracluster correlation coefficient? Crucial concepts for primary care researchers." Ann Fam Med 2(3): 204-208. |

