| 16.  a. Presentation and, if applicable, explanation of the inclusion and exclusion criteria | Inclusion criteria:  Adult patients with atraumatic abdominal pain  Capacity to consent (self or through a legal representative / carer / guardian)  Module 5: For semi-structured interviews, staff members (e.g. physicians) of the respective ED who have used the novel APU app will be interviewed.  For the participant observations, individual patients will be observed.  Exclusion criteria:  Obvious trauma or accident as cause of abdominal pain  Presence of shock or sepsis (qSOFA ≥ 2) on admission to the emergency department.  Module 5: semi-structured interviews: Experts who have not used the APU app.  Participatory observations: None. |
| b. **Study information** (information about who informs - verbally and written - and indication of how much time remains between information and consent (=reflection period) (written information as an attachment). | Due to the heterogeneity of the treatment processes of patients with atraumatic abdominal pain in the ED, the reflection period cannot be quantified. For this reason, potential study participants are first informed about the study verbally and in written form by the study team after the initial assessment in triage. The reflection period continues until contact is made with the attending physician. The treating physician informs the patient again and gives the patient further time to think about participation until the start of treatment. Study participants have sufficient time to ask questions. A longer reflection period cannot be granted, as the intervention is linked to the treatment in the ED and the study is not directly invasive in nature. Patients are informed about the risks (see point 11c).  Module 5: Experts will be informed in written form with study information about potential participation in semi-structured interviews (e.g. via e-mail or in study kick-off meetings) (see appendix X). A reflection period between information and consent will at least be 24 hours. |
| c. **Informed consent** (written as appendix) | A consent form is used for the study. In it, the participants declare their voluntariness and their consent to participate in the study (see Appendix A).  A separate consent form will be used for the expert interviews in Module 5 (see Appendix X). |

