| 25. Documentation procedure:  - If applicable: reference to CRFs  - Indication of data to be collected  - Sample handling  - Retention / archiving (incl. time limits)  - Access to data and samples | The data collection and the selection of the instruments to be used are based on international standards and are developed in a multidisciplinary process. The final data collection forms will be submitted later.  Collection of primary data happens decentralised in 10 clinics for 2.000 patients. The primary data are to be recorded in electronic case report forms (CRFs) and subsequently merged centrally. The consolidation is done via the data entry and management software secuTrail. A scientific documentalist is planned for the development of data collection instruments, electronic implementation, pseudonymisation, data merging and extraction, data monitoring, data cleaning and plausibility checks. The described evaluation-specific data on emergency admissions and hospital stays will be collected (primary data), and secondary data will be processed. Secondary data will be made available both, the hospital information systems as well as the participating health insurance company. Within the framework of the project, a central, relational database will be set up in which primary and secondary data will be made available in pseudonymised form. The scientific staff of the participating evaluating institutes, as well as the biometrician of the project, are involved in all phases of data collection, processing and evaluation. Quality assurance measures include the training of staff in data collection and technical support for the implementation of electronic data collection on site in the participating EDs, as well as monitoring of data entry and quality on site and centrally.  Two study physicians per study center (n=20) who have used the APU app / process will be interviewed with semi-structured interviews. The only documents recorded are the consent forms for interview participation. Study physicians will be recruited during staff training for the APU app or by e-mail as a letter inviting them to take part in the study with study information (e.g. information on the objective, background and the study protocol): Information about the objective, the background, data protection regulations of the study, as well as an explanation of the interview procedure). The interview will be recorded as an audio file. No personal identifying data of the physicans (or of patients through interview answers) will be collected. The audio files will be transmitted to the transcription company in accordance with data protection regulations, transcribed and transmitted back to the Institute of Medical Sociology and Rehabilitation Research. Interview transcripts are stored in anonymized form with restricted access on the servers of the Charité. The audio files of the interviews will be deleted after receipt of the interview transcripts by the Institute of Medical Sociology and Rehabilitation Research or after completion of the transcription process by the contracted transcription company. A commissioned processing agreement is concluded between the transcription company and Charité in accordance with Art. 28 DSGVO to carry out the transcription of the audio files. Access to this data is only permitted to the responsible staff member in the APU project.  For the participatory observations, n=25 patients will be observed during ED treatment. All data will be collected anonymously by study staff from the Institute of Medical Sociology and Rehabilitation Research, i.e. no personal data will be entered into the observation records, but the application of the new form of care in the "real-life" setting, as well as possible influencing contextual factors (e.g. ED procedures, communication structures, patients, staff, etc.) will be observed and recorded. The anonymous protocols are stored and analysed at the Institute for Medical Sociology and Rehabilitation Research.  Only the principal investigator of the study, as well as the staff in charge of data management, have access to the study data.  The study data will be analysed for up to 2 years after the end of the study funding.  The study data will then be kept for 10 years and then deleted. A corresponding data protection concept is being developed with the official data protection officer of the Charité and other responsible bodies. |

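### Pain at ED discharge is a primary endpoint, but the protocol specifies no pain score before treatment; one NRS item on arrival, in both phases, would protect the comparison cheaply

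*Protocol*

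**What the plan says.** Protocol section 4 lists the primary outcomes as "Acute pain score at discharge from the ED, patient satisfaction at discharge from the ED, duration of treatment in the ED".

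Section 10, Module 1, fixes when patients report: "Control and intervention groups will be interviewed via tablet computer (if necessary as paper-pencil) upon discharge from the ED (survey t0"), with a ward survey up to 72 hours after first ED contact for patients who cannot be reached in the ED, and a second survey (t1) after 30 days. The pain measure belongs to these surveys: "The analyses include current pain score (numerical rating scale (NRS").

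Module 2 gives an open list, "Clinical parameters (e.g. vital signs, previous illnesses, onset of pain, accompanying symptoms, medication history"). It includes the onset of pain but not its intensity on arrival. Module 3 (hospital information system) is also described by examples and draws on whatever data the hospital holds. Section 25 adds: "The final data collection forms will be submitted later".

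On analysis, section 15 assumes that "there are random cluster effects, fixed time effects, but no interactions between cluster and time", and remarks that the power leaves room to adjust for "potential confounders such as age and gender".

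On enrolment, section 16b states that "potential study participants are first informed about the study verbally and in written form by the study team after the initial assessment in triage"; the treating physician then informs the patient again. Under section 17, control patients are recruited until the site starts the intervention, and intervention patients afterwards. Section 19 allows the study physician to be the treating physician.

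**The concern.** Pain intensity on arrival is the natural baseline for pain intensity at discharge. Here clusters are randomised to a switching time and patients are not. Staff who know the site's phase inform patients and seek consent, so the kind of patient enrolled can change when the pathway starts. If patients recruited after the switch arrive with less pain, discharge pain looks better whatever the pathway does; if they arrive with more, a real benefit is hidden.

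The bias matters in both directions. Section 4 also counts shorter treatment with unchanged patient-reported outcomes as an improvement, so a real worsening in discharge pain could pass as unchanged if milder cases were enrolled after the switch.

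This is a data-collection matter before it is an analysis matter. An analysis plan can choose among collected variables but cannot adjust for one that was never recorded. All 10 sites start in the control phase, so the scores lost first would be those of control patients.

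**Working it through.** **1. The plan's own figures (section 15).**
- 2,000 × 0.85 = 1,700 evaluable; 1,700 / 2.71 = 627, so 313 per arm; α* = 0.05/3 = 0.0167.
- The Hussey-Hughes variance for 10 sites, 5 steps, 6 periods and ICC 0.02, divided by that of an individually randomised trial of the same size, is 2.716 (stated 2.71).
- Endpoint 1 (δ = 0.341): n = 182 per group for 80% power (stated 183; the 80% target is inferred); power at 313 per arm 96.9% (stated 96%).
- Endpoint 3 (δ = 0.499): n = 86 (stated 86); power above 99.9% (stated 99%).
- Section 15 calls endpoints 2 and 3 patient-reported, so discharge pain is one of them. Both carry a stated power of 99%.

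**2. What the planned model leaves uncorrected.** Fixed time effects absorb a case-mix shift common to all sites. Random cluster effects deal with stable differences between sites. A shift within a site that coincides with its switch is neither of these and enters the treatment effect.

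**3. Size of the bias.** Assumptions, not in the documents: d = switch-related difference in mean arrival pain, in SD; r = correlation of arrival with discharge pain.
- Bias in discharge pain: b = d × r.
- SE = √(2/313) = 0.0799; critical value z = 2.394 for two-sided 0.0167.
- False-positive probability = Φ(b/SE − z) + Φ(−b/SE − z).

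| d | r | b (SD) | b/SE | false-positive probability |
|---|---|---|---|---|
| 0.1 | 0.3 | 0.03 | 0.38 | 2.5% |
| 0.1 | 0.5 | 0.05 | 0.63 | 4.0% |
| 0.2 | 0.3 | 0.06 | 0.75 | 5.1% |
| 0.2 | 0.5 | 0.10 | 1.25 | 12.7% |

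If pain is the endpoint with δ = 0.499, the largest bias shown is 0.10/0.499 = 20% of the planned effect.

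**4. Size of the precision gain.** Adjustment multiplies the variance by about 1 − r². The more careful figure reduces only the within-cluster variance, 0.98 × (1 − r²), keeps the between-cluster variance at 0.02, and recomputes the stepped-wedge variance.

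| r | 1 − r² | 313/(1 − r²) | stepped-wedge variance ratio | effective n per arm |
|---|---|---|---|---|
| 0.3 | 0.91 | 344 | 0.919 | 341 |
| 0.5 | 0.75 | 417 | 0.772 | 406 |
| 0.6 | 0.64 | 489 | 0.668 | 469 |

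The simple formula gives a variance reduction of 9% to 36%; with the between-cluster component it is 8% to 33%.

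**The case against.** The strongest reply is that this argues from silence. The Module 2 and 3 lists are examples, the collection forms are still to come, and the questionnaires are in appendices not at hand. A reader might infer that the protocol plans no arrival pain score. The documents support only the statement that none is specified. That part of the objection stands, but it does not secure a standardised score at all 10 sites in both phases.

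A reader might also infer that adjustment is confined to age and gender. It is not: those two are examples in a remark about power, and the covariate set is ordinarily left to the analysis plan. The covariate list alone is no defect.

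A third tempting reading is that the pain endpoint lacks power. The stated figures say otherwise, so the gain in precision changes no conclusion about power.

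Finally, other severity variables are listed (vital signs, previous illnesses, accompanying symptoms, blood parameters, diagnoses), and patients are identified by the same leading symptom in both phases. These would allow partial adjustment, so it would be too strong to say that case mix could not be separated from treatment effect at all. None of them, however, measures pain intensity before treatment.

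**Conclusion.** The point holds as an inexpensive improvement, not as an error in any stated figure. As written, the protocol leaves a primary endpoint without a specified baseline, in a design where patients are enrolled after their site's phase is known. A switch-related shift in arrival severity would pass through the planned time and cluster effects.

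The size is illustrative. Type I error of about 2.5% to 13% against a nominal 1.7% rests on an assumed imbalance of 0.1 to 0.2 SD and an assumed correlation of 0.3 to 0.5. The documents do not show that such an imbalance will occur, and the upper figure is the least favourable corner of that range, not a forecast. The calculation also treats the trial as its RCT equivalent of 313 per arm. Protection against bias is the reason to act, and precision is secondary. Timing matters because a score not collected in the control phase cannot be recovered.

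**What to change.** In section 10 (Module 1 or Module 2) and in the pending eCRF, specify one NRS pain item at triage or at the first contact with the study team, before treatment, with the same wording and timing in both phases and at all sites. State in section 15, or in the analysis plan, that this score enters the discharge-pain model as a covariate. Settle this before control-phase enrolment begins.

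The cost is one question per patient at a contact that already takes place, one eCRF field and one covariate. Some arrival scores will be missing, so the analysis plan should say how these are handled. The change does not remove selection on factors that remain unmeasured.
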